## Study synopsis

|                    |                                                                                                                                                                                                                                                                                                                                                                                                                                                                                                                                           |
|--------------------|-------------------------------------------------------------------------------------------------------------------------------------------------------------------------------------------------------------------------------------------------------------------------------------------------------------------------------------------------------------------------------------------------------------------------------------------------------------------------------------------------------------------------------------------|
| Title              | Financial Toxicity in Cancer Patients Treated with Radiotherapy – a jDEGRO Confirmatory Cross-Sectional Study                                                                                                                                                                                                                                                                                                                                                                                                                      |
| Version            | v1.0 21.03.2022                                                                                                                                                                                                                                                                                                                                                                                                                                                                                                                           |
| Study coordinators | 
[name] 
 [contact]; [contact]
 
Vice coordinators:
 [name] , [contact]
 [name] , [contact]
 
 Klinik für Strahlentherapie, UKSH Campus Kiel
 [name]
 
 Klinik für Strahlenheilkunde, Universitätsklinikum Freiburg
 [name]
 |
| Study design       | Multicenter, non-interventional, confirmatory, cross-sectional study (anonymous questionnaire)                                                                                                                                                                                                                                                                                                                                                                                                                                            |
| Study population   | 
Inclusion criteria:
 
 
• Cancer patient about to complete (+/- 2d) a course of radiotherapy
 
• Ability to understand and complete the questionnaire
 
• > 18 years
 
• Patient gave informed consent
 
 
Exclusion criterion:
 
 
• Patient has already participated in the study for another course of radiotherapy
 
                                                                        |
| Patient number     | At least 504 patients based on sample size calculation                                                                                                                                                                                                                                                                                                                                                                                                                                                                                    |
| Research questions | 
Primary:
 
 
• Confirmation of the prevalence of financial toxicity
 
• Confirmation of risk factors for financial toxicity
 
 
Secondary:
 
 
• Exploration of additional variables as risk factors for financial toxicity (e.g. distress, duration of radiotherapy)
 
• Association of financial toxicity and patient satisfaction
 
                                                                    |
| Statistics         | Confirmatory for primary, and exploratory for secondary research questions                                                                                                                                                                                                                                                                                                                                                                                                                                                                |
| Data protection    | Anonymous data acquisition                                                                                                                                                                                                                                                                                                                                                                                                                                                                                                                |
| Time frame         | 
 
• Data acquisition for a 60-day period from May or June 2022
 
• Data analysis until October 2022
 
                                                                                                                                                                                                                                                                                                                                                                                |
| Funding            | none                                                                                                                                                                                                                                                                                                                                                                                                                                                                                                                                      |

### **Registration**

This study will be registered prior to enrollment of the first patient in the “Open Science Framework” ([www.osf.io](http://www.osf.io)). Furthermore, the study will be registered on the German Clinical Trials Register (DRKS) and we will apply for a registration number of the ARO (*Arbeitsgemeinschaft Radiologische Onkologie*).

### **Financial Support**

There is no external funding source or sponsor.

### **Acknowledgment**

We acknowledge statistical counseling by [name], Institute of Medical Biometry and Statistics, University Hospital Freiburg.

## **Amendments**

Amendments from protocol v1.0 (21.March.2022) to protocol v2.0 (15.Feb.2025) are highlighted in yellow.

# 1 Introduction

Cancer patients face increased costs due to the disease or its treatment. Costs may be direct in terms of increased expenditures or indirect in terms of loss of income. This objective financial burden may cause subjective financial distress which in turn may result in financial toxicity (1). Financial toxicity has been linked to suboptimal treatment outcomes and patient satisfaction (2,3). Although financial toxicity has been studied extensively in the US, it has also been described in health care systems with public funding such as in Germany (4).

Radiotherapy is a major component in the treatment of cancer as approximately one out of two cancer patients receives radiotherapy at least once during the disease trajectory (5). Patients treated with radiotherapy face specific circumstances due to their treatment. This includes local side effects which may require topical supportive care which is often not reimbursed or also long treatment courses of up to 7 weeks. In this light, radiotherapy may cause both, increased direct costs as well as loss of income which may lead to financial toxicity. Yet only small exploratory studies have investigated financial toxicity in cancer patients treated with radiotherapy ([name] et al. 2022, accepted, *Strahlenther Oncol.*). A better understanding of the prevalence and associated risk factors of financial toxicity is desirable to mitigate its potentially deleterious effect on treatment outcomes and patient satisfaction.

## 2 Methods

This is a cross-sectional, multi-center survey-based study. The questionnaire will be handed out to every patient meeting the eligibility criteria along with a study information. Informed consent is given if a patient returns the questionnaire in a sealed envelope. The survey is anonymous to ensure data protection.

Participating jDEGRO centers are (jDEGRO=junge DEGRO [Deutsche Gesellschaft für Radioonkologie]):

- University Hospital Freiburg, Department of Radiation Oncology, Freiburg
- University Hospital Schleswig-Holstein, Department of Radiation Oncology, Kiel
- University Hospital Cologne, Clinic and Policlinic for Radiation Oncology, Cyberknife and Radiotherapy, Cologne
- University Hospital Jena, Department of Radiotherapy and Radiation Oncology, Jena
- LMU University Hospital, Department of Radiotherapy and Radiation Oncology, Munich
- Additional German centers may follow and will be updated on the registration database DRKS

### 2.1 Eligibility criteria

Inclusion criteria are i.) cancer patient about to complete (+/- 2d) a course of radiotherapy, ii.) ability to understand and complete the questionnaire, iii.) >18 years, and iv.) patient gave informed consent.

The exclusion criterion is participation in the same study for another course of radiotherapy.

### 2.2 Outcomes and variables

All data will be retrieved from a questionnaire. The questionnaire was pilot tested on five voluntary, potentially eligible patients in March 2022. Thereafter, subtle changes to the layout were implemented. Furthermore, an additional sex category (“diverse”) was added.

Outcome data originate from two questions on objective financial burden (additional costs and loss of income in the context of radiotherapy), one question on subjective financial distress (question 28 of the EORTC QLQ-C30), and a single question on patient satisfaction with radiotherapy (Numeric Rating Scale 0-10, modified based on (6)). At the conception of this study, there was no validated German measure to assess financial toxicity in terms of a single effect size. Therefore, we relied on subjective financial distress as surrogate parameter for financial toxicity as in a previous study ([name] et al. 2022, accepted, Strahlenther Oncol.).

Variables include sociodemographic data (sex, age, marital status, education level, health insurance, exemption from copayments in social health insurance), data on the disease and radiotherapy (type of cancer, duration of radiotherapy, concomitant chemotherapy, out- vs. inpatient), data on occupation and finances (employment status, net household income), patient

distress (NRS distress thermometer (7)), and overall health-related quality of life (question 29 and 30 of the EORTC QLQ-C30).

### **2.3 Statistical analysis plan**

One primary research question is the confirmation of the overall rate of financial toxicity per subjective financial burden (question 28 EORTC QLQ-C30) as detected in a previous exploratory study ([name] et al. 2022, accepted, Strahlenther Oncol.). This study employed the same eligibility criteria. The questionnaire from this study was only slightly modified for the present study. Questions on outcomes or variables for the primary research questions were not modified. In the previous study, overall 31% of the patients reported subjective financial distress ([name] et al. 2022, accepted, Strahlenther Oncol.).

To confirm this overall prevalence of financial subjective distress, we determined a sample size of  $n = 329$  based on the expected prevalence of 31% and assuming a precision of the estimate of 5%. Accordingly, if the prevalence of subjective financial distress falls into the 95% binomial exact confidence interval of 26.04-36.31%, this primary research question will be regarded as confirmed. The subgrades of subjective financial distress were rated by patients as 21% “a little”, 6% “quite a bit”, and 4% “very much” in the previous study. Yet of note, we considered the endpoint to be binary (absence/presence of financial distress) to determine the necessary sample size for estimating the prevalence.

Another primary research question is the confirmation of risk factors of financial toxicity per subjective financial distress as shown in the previous study ([name] et al. 2022, accepted, Strahlenther Oncol.). Statistically significant risk factors included lower net household income (OR= 0.28;  $p = 0.01$ ), higher direct costs (OR= 2.78;  $p = 0.021$ ), and higher loss of income (OR= 2.48  $p = 0.025$ ) per multivariate ordinal regression. Active employment status (OR= 16.96;  $p = 0.067$ ) and lower health-related quality of life (OR= 0.51;  $p = 0.058$ ) were also associated with higher subjective financial distress per multivariate ordinal regression.

To be able to confirm these risk factors, we conducted a sample size calculation based on a logistic regression model using G\*Power Version 3.1.9.6 (Faul et al. 2007,2009) since sample size determination for ordinal regression models requires potentially complex simulation approaches (8,9). We used a conservatory approach by calculating the sample size for the smallest response subcategory of the dependent variable (“very much” subjective financial distress), which was reported by 4% of the patients based on the previous study as mentioned above. We conducted the sample size calculation based on a type I error of  $\alpha = 0.05$ , a power of 0.8, an odds ratio for the expected effect size of 0.5, and a correction factor for covariates (for details, see G \* Power 3.1 manual, p. 70, ‘ $R^2$  other X’), the resulting sample size was  $n = 504$  patients for a two-sided z-test. If the risk factors mentioned above significantly predict the extent of subjective financial distress per ordinal regression analysis, these risk factors will then be regarded as confirmed in the setting of our study.

Secondary research questions include the exploration of additional variables as risk factors for financial toxicity (e.g. distress, duration of radiotherapy) as well as the exploration of an association of subjective financial distress and patient satisfaction.

Participation rate will be described based on returned questionnaires and the number of cancer patients that finished a course of radiotherapy during the study period. This approach underestimates the participation rate as also potentially ineligible patients (e.g. unable to understand questionnaire) will be included in the latter number. However, this approach appears reasonably feasible due to the large overall patient numbers in each center.

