## **2.4    *Duration of the study***

To achieve the largest planned sample size of 504 patients we plan patient accrual during two consecutive months. This assumption is based on five participating centers, 2.000 treated patients per year per center, and a participation rate of 30% resulting in 600 patients after 60 days of accrual. The participation rate of 30% is a conservatory estimate based on the previous study (53.3%) and based on the underestimating definition of participation rate (as mentioned in chapter 2.3).

In case the planned sample size will be achieved earlier, accrual will continue to complete two months of accrual in order to facilitate additional exploratory analyses. In case the planned sample size should not be achieved after two months, accrual will continue until the planned sample size will be achieved if feasible in a reasonable amount of time. All centers will report the number of included patients on a weekly basis to the study coordinators.

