### 5.2 Methods

This is a secondary analysis with pooled data from two studies. Data from cancer patients at the end of a course of radiotherapy will be used as collected for the primary study of this protocol. In total, 1075 patients were recruited of which 1052 responded to global quality of life. The general population cohort, including 1006 individuals in Germany, is based on [name] et al. (15).

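### The prevalence confirmation band gives the earlier study's 31% no sampling error, so its 95% label does not say how often two agreeing studies would be called confirmed

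*Protocol*

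**What the plan says.** Section 2.3 makes it a primary question whether the rate of subjective financial distress seen in an earlier exploratory study is confirmed. The reference value is a point estimate: "In the previous study, overall 31% of the patients reported subjective financial distress". The sample size of 329 is "based on the expected prevalence of 31% and assuming a precision of the estimate of 5"%. The decision rule follows directly: if the new prevalence "falls into the 95% binomial exact confidence interval of 26.04-36.31%, this primary research question will be regarded as confirmed".

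The protocol gives neither the size of the earlier study nor a confidence interval for its 31%. The Introduction describes the evidence base in words only: "Yet only small exploratory studies have investigated financial toxicity in cancer patients treated with radiotherapy". The citation attached there is to an accepted 2022 report, as is the citation attached to the 31% in section 2.3.

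The number of patients is larger than 329 throughout. The synopsis asks for "At least 504 patients based on sample size calculation", section 2.4 expects accrual "resulting in 600 patients after 60 days of accrual", and the amended section 5.2 reports: "In total, 1075 patients were recruited of which 1052 responded to global quality of life".

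**The concern.** Asking whether a second study confirms the rate found in a first compares two estimates, each with sampling error. The rule allows for the error of one only. It draws the scatter expected of a new sample of 329 around a centre that is treated as exact.

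If the earlier sample was small, its 31% may lie several points from the true rate by chance. A larger new study does not cure this, because the error sits in the centre of the band. A new result outside the band could then be reported, on a primary question, as a failure to replicate although the two studies are compatible. The label of a 95% interval invites the reader to think that this happens about one time in twenty, and nothing in the rule secures that.

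**Working it through.** **Inputs.** Prevalence 0.31, precision 0.05, n = 329 and band 26.04–36.31% (section 2.3). New n of 504 (synopsis), 600 (section 2.4) and 1,075 (section 5.2; the number with an answer to question 28 is not given and may be slightly lower). The earlier study's size, n0, is **assumed**, because the protocol does not state it.

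**1. The protocol's own figures.** Sample size: 1.96² × 0.31 × 0.69 / 0.05² = 328.7, so 329. The exact (Clopper–Pearson) 95% interval for 102/329 is 26.04–36.31%. Both reproduce. The arithmetic is right, and the earlier study's size plays no part in it.

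**2. The rule if 31% were known exactly.** The exact binomial chance of falling outside the band is 4.3% at n = 329, 1.3% at 504, 0.7% at 600 and 0.03% at 1,075. So even under the rule's own premise, the 95% label fits only n = 329.

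**3. The rule if the earlier 31% carries error.** Let both studies sample the same true prevalence of 31%. Non-confirmation means that the new estimate differs from the earlier one by less than 26.04 − 31 = −4.96 points or more than 36.31 − 31 = +5.31 points. The standard error of the difference is

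s = √[0.31 × 0.69 × (1/n0 + 1/n)]

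and P(not confirmed) = Φ(−0.0496/s) + 1 − Φ(0.0531/s).

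Example, n0 = 100 and n = 504: s = √[0.2139 × (0.01 + 0.00198)] = 0.0506. The limits lie at z = −0.98 and z = 1.05. The chance is 0.164 + 0.147 = 0.31.

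| Assumed n0 | new n = 329 | new n = 504 | new n = 1,075 |
|---|---|---|---|
| 100 | 33% | 31% | 29% |
| 200 | 22% | 18% | 15% |
| 300 | 16% | 13% | 9% |
| 500 | 12% | 8% | 4% |
| 1,000 | 8% | 4% | 1% |

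An exact double binomial sum and a beta-binomial predictive calculation agree within about 1 point.

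**4. Where the problem stops.** The chance falls to 5% at an n0 of about 830 for new n = 504, 650 for 600 and 440 for 1,075. For new n = 329 it takes about 6,400.

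**5. What both errors would require.** A 95% prediction range for the new estimate has half-width 1.96 × s. At new n = 504 this is ±9.9 points for n0 = 100, ±7.6 for 200, ±6.6 for 300 and ±5.7 for 500, against about ±5 in the protocol. With n0 = 100 the earlier study's own exact interval (31/100) would be 22–41%, wider than the band that judges the new study.

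**6. Would a two-sample rule alone be better?** Assume an earlier 31/100 and new n = 504. The 95% CI for the difference includes 0 for any new prevalence from 21.4% to 40.9%. If the true prevalence were 38%, that rule would miss the discrepancy about 91% of the time, whereas the stated band would pass it 23% of the time. At a true 40% the figures are 67% and 5%.

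**The case against.** The best defence is that section 2.3 never promises a rate of false non-confirmation. It sets a precision of 5 points and derives a numerical range from it, which can be read as an agreed tolerance around a benchmark. On that reading, if the earlier study drew 31% by chance when the truth is 25%, non-confirmation is the correct answer, because the published figure did not hold up. This stands, and it is a reason to keep the band. But the protocol does not call it a tolerance or justify ±5 points as one. It calls it a 95% exact confidence interval, and that label is what misleads.

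A reader might go further and infer that agreeing studies will be declared unconfirmed far more often than 5% of the time. The protocol does not support that without a condition. The earlier n is not given, *small* is not quantified, and at n0 = 500 with 1,075 new patients the chance is 4%.

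A reader might also conclude that the band should give way to a rule that withholds confirmation only when the two-sample CI excludes 0. That would treat lack of significance as agreement and would confirm more easily the weaker the earlier evidence is (step 6).

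Finally, recruitment is complete, so replacing a prespecified primary criterion now would be a change made after data collection. That also stands and limits the remedy to added reporting and corrected wording.

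**Conclusion.** The point holds in a limited form. The confirmation rule treats an estimated 31% as exact, and its 95% label does not describe how often two agreeing studies would be called confirmed. The structural part needs no assumption, because the earlier study's size is absent from both the rule and the protocol. The size of the effect does depend on an assumption. Over the three new sample sizes it is 29–33% for an earlier n of 100, 15–22% for 200, 9–16% for 300 and 4–12% for 500, given that both studies sample the same 31%. It is therefore material only if the earlier study was small. The Introduction's wording suggests that it was, but does not establish it. The figures of 329 and 26.04–36.31% are correct. The fault lies in how the band is labelled and in what may be concluded from a result outside it.

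**What to change.** In section 2.3:

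- Report the new prevalence with its own 95% CI, at the actual number of respondents, as the main result.
- Add the difference (new minus previous) with a 95% CI computed from the counts of both studies. State the earlier n beside it, and label this analysis as added after recruitment.
- Keep the prespecified 26.04–36.31% band, but describe it as a fixed agreement range of about ±5 points around 31%, not as a 95% criterion.
- Do not report a result outside the band as a failed replication unless the two-sample CI also excludes 0.
- State that a difference CI including 0 is not in itself confirmation, and always show its width.

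The cost is a few lines of text and one two-sample interval, with no new data from patients. The earlier study's counts must be taken from its publication. The downside is that, if that study was small, the replication statement becomes visibly less sharp.
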